## Abstract

**Background:**

Dietary interventions including consumption of flavonoids, plant compounds found in certain foods, may have the ability to improve fatigue. However, to date, no well-designed intervention studies assessing the role of flavonoid consumption for fatigue management in people with MS (pwMS) have been performed. The hypothesis is that the consumption of a flavonoid-rich pure cocoa beverage will reduce fatigue in pwMS. The aim of this study is to determine the feasibility and potential outcome of running a trial to evaluate this hypothesis.

**Methods:**

Using a randomised (1:1) double-blind placebo-controlled feasibility study, 40 men and women (20 in each trial arm) with a recent diagnosis (< 10 years) of relapsing and remitting MS (RRMS) and who are over 18 years of age will be recruited from neurology clinics and throughout the Thames Valley community. During a 6-week nutrition intervention period, participants will consume the cocoa beverage, high flavonoid or low flavonoid content, at breakfast daily. At baseline, demographic factors and disease-related factors will be assessed. Fatigue, activity and quality of life, in addition to other measures, will be taken at three visits (baseline, week 3 and week 6) in a university setting by a researcher blinded to group membership. Feasibility and fidelity will be assessed through recruitment and retention, adherence and a quantitative process evaluation at the end of the trial.

We will describe demographic factors (age, gender, level of education) as well as disease-related factors (disease burden scores, length of time diagnosed with MS) and cognitive assessment, depression and quality of life and general physical activity in order to characterise participants and determine possible mediators to identify the processes by which the intervention may bring about change. Feasibility (recruitment, safety, feasibility of implementation of the intervention and evaluation, protocol adherence and data completion) and potential for benefit (estimates of effect size and variability) will be determined to inform future planned studies. Results will be presented using point estimates, 95% confidence intervals and *p* values. Primary statistical analysis will be on an intention-to-treat basis and will use the complete case data set.

**Discussion:**

We propose that a flavonoid-enriched cocoa beverage for the management of fatigue will be well received by participants. Further, if it is implemented early in the disease course of people diagnosed with RRMS, it will improve mobility and functioning by modifying fatigue.

**Trial registration:**

Registered with ISRCTN Registry. Trial registration No: ISRCTN69897291; Date April 2016

## Background

Fatigue is one of the most common and debilitating symptoms experienced in people with MS (pwMS), and it is thought that as many as 53–90% of pwMS suffer from fatigue [1].

Currently, there are no highly effective treatments for fatigue in MS; however, simple lifestyle interventions including diet approaches may be beneficial for reducing the extent of fatigue [2].

The physiological causes of fatigue are complex, including neural, inflammatory and metabolic mechanisms, and can result in further changes including increased cytokine production, oxidative stress and altered glutamate/glutathione levels in the brain, all thought to contribute to fatigue [3–7]. Certain compounds in foods called flavonoids may be used to exert drug-like effects in reducing the severity of fatigue by tackling these mechanisms, and these foods are becoming increasingly popular for their alleged ubiquitous benefits on health, the ageing process and neurological function [8].

Dark chocolate containing 70% or more cocoa solids is well known for its high antioxidant and flavonoid content. Over a 4-week period, dark chocolate consumption has been shown to improve fatigue in those with chronic fatigue syndrome (CFS) which could part due to the improvements in immune function that is often seen with the condition [9]. Also, results from a small randomised controlled pilot study and using a short-term cocoa intervention suggested an increase in sleep quality and reduction in fatigue [10].

Alterations in inflammatory and immunological function have been shown to precede relapses in those with relapsing and remitting MS (RRMS) [11] and have been thought to contribute to the early symptoms of fatigue [12–14]. This has therefore raised the question as to whether alleviating these markers may improve the fatigue experienced early on in those with the disease and improved mobility and physical activity [15, 16].

This study sets out to determine the potential benefit and feasibility of implementing a flavonoid dietary intervention that was co-designed with pwMS. We propose that a single drink of flavonoid-rich cocoa taken each morning over a 6-week period will be feasible and acceptable for pwMS. We will also estimate the variation and change in fatigue to allow for a power calculation to be made for a larger trial. In addition, there is a process evaluation of both quantitative and qualitative components. The study uses a randomised, parallel group controlled design where participants will either be supplied with cocoa rich in flavonoids or a low-flavonoid cocoa drink that looks and tastes the same.

### Objectives

To determine whether the current study design is feasible to undertake, and to estimate the potential benefit and number of participants needed for a phase III trial, the following key objectives will be assessed from results of this study:The acceptability of the study design and dietary intervention to participantsRecruitment rate and reasons for non-recruitmentFollow-up rate and reasons for loss to follow-upLevel of adherence to the protocol, including the process of randomisationA parallel process evaluation to explore participant acceptance, potential concerns and overall process flow of the proposed interventionData acquisition rate, amount of missing data and reasons for lossTo determine the variability and effect size of the outcome measures, especially on fatigue.

## Methods

### Setting

All testing will take place at the Oxford Brookes University (OBU), Oxford, UK, except for home visits in which participants have the option for researchers to visit their homes to collect measures. The intervention will be self-directed and take place in the home of each participant. Testing will take place in the morning between 7.30 and 10 a.m.

### Recruitment

PwMS will be recruited from the Oxford University Hospitals National Health Service (NHS) Trust (John Radcliffe Hospital site), Milton Keynes Hospital, Royal Berkshire Hospital or Buckingham Hospital by nurses and clinicians at each site who work with MS patients, through a list of those who have consented to being contacted about clinical trials. Potentially eligible participants who are interested in the study will have their contact details collected by the lead researcher who will provide further information. Local MS Society branches will also be made aware of the trial and given contact details, and an advertisement for the study along with the participant information sheet will be made available on the MS Society website. Individuals will then be able to self-refer to the study.

### Trial design

This is a mixed methodology, randomised double-blind placebo-controlled feasibility trial and process evaluation. As a feasibility trial, aspects of feasibility will be determined and estimates of effect size and measured variability will be calculated to inform future planned studies. The intervention will last a total of 6 weeks. Participants will be assessed at baseline on enrolment into the trial. Randomisation to allocate participants to either intervention or control group (1:1) will be performed immediately following the baseline assessment, and intervention delivery will begin directly after the baseline assessment. Participants will then be reassessed at 3 and 6 weeks (assessments 2 and 3, respectively) after the baseline. At assessment 2, the lead researcher accompanied by one of the research team will offer to travel to the home of the participants to take measures, if they so wish (Fig. 1). This is to reduce patient burden with the aim to increase recruitment and retention rate.

**Fig. 1 Fig1:**
[figure not shown]
Trial schema and participant flow diagram

### Participants

Participants will be considered eligible for the study if they present with the following criteria:Aged 18 years or more with a new clinical diagnosis of RRMS within the past 10 yearsThose who are treatment naïve or taking first-line disease-modifying treatments (DMTs) (glatiramer acetate, interferon beta, teriflunomide and dimethyl fumarate, but also alemtuzumab and Tysabri if used as first-line treatments)No relapse or sudden change in their MS symptoms within the previous 3 monthsDo not have contraindications to providing a blood sampleNo contraindications to tolerating the cocoa drinkA fatigue measure of greater than 4 on the Fatigue Severity Scale (FSS) [17]No other conditions that may be associated with fatigue, e.g. anaemiaNo clinical diagnosis of depressionAn Expanded Disability Status Scale (EDSS) score of < 4.5Sufficient mental capacity to consent as determined by the researchersAble to walk with or without a walker for at least 16 mNo condition affecting the central nervous system other than MS (however, migraine is allowed)Not pregnant or lactatingNo objection to the researchers contacting their general practitioner and neurologist

Participants must also not be on any other clinical trial during the study.

### Consent

Participants will be emailed or personally administered an information sheet by clinicians at one of the hospital sites or by a member of the research team and given at least 24 h to consider the information. An eligibility check will be performed over the telephone by one of the researchers. During the telephone call and at the baseline assessment, potential participants will be allowed to ask questions if they wish to participate in the study, and enrolment into the trial will be immediately allocated. Informed consent will be obtained by members of the research team at the baseline assessment, who will be trained in taking consent and in good clinical practice. Recruitment began in May 2016.

Withdrawal of consent will have no detrimental impact on current and future treatment, and those taking consent will ensure that participants fully understand this. If a participant was to lose his/her capacity to consent during the trial, the participant will be withdrawn, no further procedures will be carried out on them and no new personal data will be collected. Data that has already been collected in relation to the participant may be retained and used for the purposes for which consent has already been given, provided they are effectively anonymised and no longer identifiable to the research team.

### Retention

We will make every effort to reduce loss to follow-up. One primary contact within each centre will contact all participants and act as liaison with the blinded assessor. The primary contact person will obtain information about the participants’ preferred method of contact (text, telephone, email and letter) and contact them using this preferred method when possible. They will also ask the participant for details of a nominated person who can be contacted if the team is unable to make contact with them, and we will retain details of the participant’s general practitioner. Contact details will be updated if applicable at each assessment. All appointments will be made at the research participant’s convenience wherever possible. If an appointment is missed we will try to rearrange this on two more occasions.

### Screening

A screening log will be kept at OBU where details of numbers of people who were approached about the trial, eligibility and whether consent to be contacted was given or declined will be recorded. A log of any individuals, who declined at the initial consent stage, or consented but failed screening, will also be kept. A case report form (CRF) will be completed for all consented individuals, which will include details of nominated persons (e.g. mother or friend) to facilitate participant follow-up.

### Outcomes

The primary aim of this study is to assess feasibility of the dietary intervention in terms of adherence, safety and process. This will be achieved through the documentation of adherence and any adverse events (AEs), as well as any health-related changes such as gastrointestinal disturbances that may occur during the intervention period. Duration of participation and dropout from the intervention will also be recorded. In order to assess benefits, a range of outcomes will be obtained. Outcome measures includeLevels of physical activity: wearable activity monitors (worn like a watch) [18] and the Physical Activity Scale for the Elderly (PASE) questionnaire [19]Dietary patterns assessed by a nutritionist: three 24-h dietary records [20]Fatigue levels: FSS, Neuro-QOL [21], and during the intervention, a Numerical Rating Scale (NRS) scored from 1 to 10, three times daily which classifies no fatigue as a 1 and very fatigued as a 10.Fatigability: performance on 6-min walk test (physical) [22] and the Adult Memory and Information Processing Battery (AMIBP; mental) [23]Blood markers of inflammation: TNF-alpha, reduced glutathione, a marker of antioxidant status and lipid peroxidationHealth descriptives: EQ5D5L [24] and the Preference-Based Multiple Sclerosis Index (PBMSI) [25], basic health questionnaire, Barthel ADL Index (BI) [26] and Hospital Anxiety and Depression Scale (HADS) [27]

Demographic factors and background factors will be assessed at baseline: medication, age, gender, level of education, type of MS, duration of disease, height, weight and leg length will be assessed at baseline. Participants will be stratified for gender and whether they are on first-line disease-modifying treatments or not.

Table 1 summarises the questionnaires that will be administered throughout the trial and at which visits these measures will be collected.

**Table 1 Tab1:** Outcome measures

Domain to be measured	Outcome measure(s)	Time required	When
Measures of overall health and questionnaires			
1. Health questionnaire and health assessment	General medicine use/health problems, etc.	10 min	1
2. Global fatigue	Neuro quality of life	5 min	1, 2, 3
3. Limitations in daily activity	Barthel Activities in Daily Living Index	5 min	1
4. Quality of life measure	EuroQOL 5D5L and Problem Based Multiple Sclerosis Index	5 min	1, 2, 3
5. Dietary recall	Monitor diet patterns	10 min	1, 2, 3
6. Consent	Verbal followed by written	10 min	1
8. Speed of information processing	The Adult Memory and Information Processing Battery	5 min	1, 2, 3
9. Depression	Hospital Anxiety and Depression Scale	5 min	1, 2, 3
10. Physical activity	Physical Activity Survey for the Elderly	10 min	1
11. Fatigue	Fatigue Severity Scale	5 min	1
Measures of activity and fatigue			
11. 6-min walk	Fatigue	6 min	1, 3
12. Accelerometer	Activity	2 weeks and 3 days throughout intervention	–
13. Numerical Rating Scale for fatigue	Fatigue	3 times daily for 6 weeks	–
Measures of plasma markers			
14. Venous blood samples	Inflammation, oxidative stress, antioxidant capacity of plasma	5 min	1, 2, 3

1 = baseline assessment; 2 = assessment 2 (3 weeks); 3 = assessment 3 (6 weeks)

### Intervention

#### Cocoa

Participants will consume the drink (intervention or control) in their homes, after a 10-h overnight fast at the same time each morning. After the consumption of the drink (18 g of cocoa in 200 ml heated rice milk), they will wait an additional 30-min period before consuming any other food or beverage. They will be instructed to take their normal medication and to follow their diet as usual. On the days when assessments take place at the university, participants will arrive fasted and will therefore not consume the cocoa that day. The cocoa drinks (intervention and control) are designed to differ only in flavonoid content (low {19 mg cocoa flavonoids} versus high {200 mg cocoa flavonoids} flavonoid content). The flavonoid-rich pure cocoa drink will be matched to the control drink for macronutrients, theobromine and caffeine and will be as identical as possible in appearance and taste to ensure double blinding. Cocoa powder will be provided in air-tight individual sachets, and participants will receive 21 packets at the baseline visit and again at assessment 2; the contents will need to be added to a mug, and heated rice milk will be added prior to consumption. Instructions on preparation will be provided to ensure all participants follow the same protocol. Unused cocoa content will be saved and collected by the researcher.

### Fatigue

Fatigue will be measured at baseline using the FSS. If participant scores a 4 or above and thus fulfils the criteria to take part in the trial, he or she will then wait 3 days before beginning the intervention. On the fourth day, the participant will begin consuming the coca drink. Directly after the consumption of the drink, participants will rate on an NRS their level of fatigue. This will be followed by two additional measures recorded at 3 p.m. and 8 p.m., daily for the 6 weeks. They will be asked to reply to the text message with a score of fatigue from 1 to 10, 1 being no fatigue and 10 being very fatigued. Smart phones will be provided to those who do not have them and collected after the trial termination, and ease and acceptability of phone use will be documented. Walking endurance will be measured a total of two times (baseline and assessment 3) using a 6-min walk test [22], and sensors will be worn to measure gait during the walk. Gait measurements will be collected via an inertial measurement unit (IMU) [28, 29] attached to the lower spine (lumbar 4 region) by double-sided adhesive tape. Participants are instructed to walk over a 14-m walkway free of obstacles at their self-selected walking speed. Walking speed will be derived from IMU data by using well-established validated algorithms [28, 29].

### Blood measures

Participants will have fasting blood samples taken by a trained phlebotomist a total of three times throughout the trial. Blood samples will be collected at OBU or at the home of the participant (assessment 2). Blood collection will be in the morning when the participant is fasted, time will be recorded at the first collection and collection for subsequent assessments will be taken within an hour of this time. Blood will be labelled and frozen for future analysis following standard operating procedures (SOPs) for storage of plasma at OBU. Fasting plasma glutathione (oxidised and reduced) will serve as a measure of adherence to the consumption of the drink throughout the trial. Changes in levels of the inflammatory marker TNF-alpha (ELISA assay kit) and lipid peroxidation (MCA reaction assay) will also be measured as markers of inflammation and oxidative stress, respectively, at the same time points. Assays for these individual markers will be purchased from Sigma-Aldrich (UK) and will be analysed using facilities available at OBU. Outcome measures will be determined from venous blood (total at each assessment no more than 50 ml) samples taken three times throughout the intervention—baseline assessments 1 and 2, after an overnight (10–12-h) fast. These measures will determine the change in metabolic parameters throughout the trial and will also allow for adverse changes made possible due to the consumption of the control drink. In addition, compliance and willingness to have blood measures taken will be documented.

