#### Adherence

Successful adherence to the intervention will be defined as at least 75% of the participants having completed cocoa consumption [33]. We will assess discontinuation of the intervention. Further aspects of adherence will be measured by the percentage of fatigue texts completed by participants and those who wore the accelerometer-axivity watches. If the proportion is less than this but greater than 65%, we will consider adjusting the intervention to increase this in future investigations. An adherence rate lower than this would require substantial changes to the intervention and therefore require further piloting.

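### Plasma glutathione is named as an adherence measure for both arms although it is also a benefit outcome and the control drink carries only 9.5% of the active flavonoid dose

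*Protocol article*

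**What the plan says.** Under Blood measures, the protocol article gives glutathione an adherence role: "Fasting plasma glutathione (oxidised and reduced) will serve as a measure of adherence to the consumption of the drink throughout the trial". The sentence covers the drink in general and is not restricted to the high-flavonoid arm.

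The Outcomes section places reduced glutathione in the list of measures obtained to assess benefit, next to TNF-alpha and lipid peroxidation. Table 1 schedules the blood samples at all three visits under the domain "Inflammation, oxidative stress, antioxidant capacity of plasma".

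The Background gives the rationale. It cites "oxidative stress and altered glutamate/glutathione levels in the brain, all thought to contribute to fatigue" and continues: "Certain compounds in foods called flavonoids may be used to exert drug-like effects in reducing the severity of fatigue by tackling these mechanisms".

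On the product, the Cocoa section says "The cocoa drinks (intervention and control) are designed to differ only in flavonoid content", specified as "low {19 mg cocoa flavonoids} versus high {200 mg cocoa flavonoids} flavonoid content". It also says "Unused cocoa content will be saved and collected by the researcher", but does not call this an adherence measure.

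The Adherence section sets the success criterion: "Successful adherence to the intervention will be defined as at least 75% of the participants having completed cocoa consumption". A result between 65% and 75% would lead to adjusting the intervention, and a lower one to further piloting. Fatigue texts and accelerometer wear are named as further aspects. Glutathione is not mentioned there, and the section does not say how consumption is ascertained.

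**The concern.** A useful adherence marker should respond to taking the product in the same way in both arms, and should not itself be an effect under study. Glutathione, as used here, is doubtful on both counts. The trial expects flavonoids to act on this pathway, and flavonoids are the one component by which the drinks are designed to differ. A marker driven by flavonoids would then register intake better in one arm than in the other.

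The double role also confounds interpretation. If glutathione does not change in the high-flavonoid arm, that could mean the drink was not taken, or that it was taken and had no such effect. One variable cannot answer both questions.

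This matters because adherence comes first in the primary aim and has its own rule for proceeding, adjusting or re-piloting. The glutathione sentence is also the only place where the article names a measurement of adherence to the drink itself.

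**Working it through.** The plan states no figure to reproduce on this point. The check has three steps.

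**1. Dose ratio.** From the Cocoa section: 19/200 = 0.095, so the control carries 9.5% of the active flavonoid dose (200/19 = 10.5-fold difference). This is a ratio of doses, not of glutathione responses.

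**2. The two roles under each possibility.**
- *Flavonoids change plasma glutathione.* Adherent controls are expected to show less change than adherent high-flavonoid participants, and may not be distinguishable from controls who drink nothing. The marker then depends on arm.
- *Flavonoids do not change it, and nothing else in the drink does.* The marker shows adherence in neither arm.
- *Both drinks move it equally through something they share.* The arm dependence disappears, but glutathione then shows nothing about the flavonoid contrast.

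In none of the three cases does one variable serve both as an even-handed adherence measure and as an informative outcome of the flavonoid contrast. Participants also keep their usual diet and medication, so glutathione could move for reasons other than the drink.

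**3. Illustration of the size, if a glutathione response were used to class people as adherent.** The documents plan no such classification, and all three inputs below are assumptions:
- A = true adherence, the same in both arms
- s = chance that an adherent high-flavonoid participant shows a response
- c = the same chance for an adherent control

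Non-drinkers are taken never to show a response. With 20 participants per arm:

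proportion classed adherent = 0.5 × A × s + 0.5 × A × c

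| A | s | c | High-flavonoid arm | Control arm | Overall |
|---|---|---|---|---|---|
| 0.9 | 1.0 | 0 to 0.2 | 90% | 0% to 18% | 45% to 54% |
| 0.9 | 0.8 | 0 to 0.2 | 72% | 0% to 18% | 36% to 45% |
| 1.0 | 1.0 | 0 to 0.2 | 100% | 0% to 20% | 50% to 60% |
| 1.0 | 0.8 | 0 to 0.2 | 80% | 0% to 20% | 40% to 50% |
| 0.9 | 0.8 | 0.8 | 72% | 72% | 72% |

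For example, row 1 at c = 0.2 gives 0.5 × 0.9 × 1.0 + 0.5 × 0.9 × 0.2 = 0.45 + 0.09 = 0.54. In the first four rows the overall figure is 36% to 60%, below 65%, although true adherence is at least 90%. The arm difference vanishes only when c = s, as in the last row.

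**The case against.** The strongest reply is that glutathione does not enter the adherence rule. The Adherence section words the criterion on completed cocoa consumption, names texts and accelerometer wear as further aspects, and does not mention glutathione. The Blood measures sentence calls it a measure of adherence, not the only one, and unused cocoa is collected anyway. All of this stands.

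Several stronger readings are tempting, and the documents do not support them:
- *Adherent controls will be counted as non-adherent, up to 20 of 40.* No cut-off or change score classifies anyone, and 20 is simply the size of the control arm.
- *The marker cannot show intake in the control arm at all.* The control contains 19 mg, not zero, and no dose-response is given. The Background also speaks of glutathione in the brain, while the trial measures plasma, so the link is looser than it looks.
- *Analyses by adherence will select on response.* No adherence-restricted analysis is planned. The primary analysis is by intention to treat, and Data management keeps the data of those who discontinue or deviate.
- *The pooled 75% rule is itself faulty.* It could be met by 20/20 controls and 10/20 high-flavonoid participants (30/40 = 75%), but that is an extreme split for drinks made to look and taste alike. The article does not rule out reporting by arm, and this is a separate matter from glutathione.

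It could also be said that linking returned cocoa to the rule is operational detail that a condensed article leaves to the full protocol. That is fair for the detail. It does not answer the point about glutathione, because the article positively assigns it the adherence role.

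**Conclusion.** The concern holds in a limited form. The article gives plasma glutathione two roles that do not fit together: adherence measure for both arms and benefit outcome. On the trial's own premise it is at risk of arm-dependent bias as an adherence measure, and it cannot separate intake from effect.

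The dual role and the 9.5% dose ratio are facts of the document. That adherent controls may be indistinguishable from non-adherent ones is an inference, which rests on flavonoids driving plasma glutathione roughly in line with dose. The 36% to 60% range shows what could happen under assumed response probabilities; it is not an estimate for this trial.

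The feasibility decision is affected only if glutathione is used to judge whether cocoa was consumed. If consumption is judged from unused cocoa, the 75%/65% rule is untouched. The point deserves correction because the change is cheap and adherence is central to the primary aim.

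**What to change.** Two changes of wording:
1. In Blood measures, describe glutathione as an outcome. If an exposure role is wanted, limit it to a supportive marker in the high-flavonoid arm and do not present it as evidence of intake in both arms.
2. In Adherence, state that cocoa consumption for the 75%/65% rule is measured from the unused cocoa already collected under Cocoa, and report it overall and by arm with 95% confidence intervals. The number dispensed is known: 21 sachets at each of two visits, 42 in all.

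No new data collection is needed. There are two costs. Returned-sachet counts can overstate intake, since a missing sachet need not have been drunk. By-arm intervals are also wide: the exact (Clopper-Pearson) 95% interval is 51% to 91% for 15/20, against 59% to 87% for 30/40 overall. The by-arm figures are therefore descriptive.
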